| **Background** | Ten percent of patients with cirrhosis develop ascites. In 90% of patients, ascites can be treated with diuretics. The management of the remaining 10% with diuretic resistant ascites is challenging. Symptoms including abdominal pain, dyspnoea, nausea, vomiting, and anorexia have a detrimental impact on the quality of life. Repeated large volume paracentesis provides only temporary improvement of symptoms. |
| --- | --- |
| **Hypothesis** | Insertion of a tunnelated peritoneal catheter (PleurX) allows repeated intermittent small volume fluid drainage at home. The treatment may improve the management of ascites and have a beneficial effect on the quality of life. |
| **Objectives** | To evaluate the beneficial and harmful effects of the peritoneal catheter (PleurX) versus repeated large volume paracentesis for patients with cirrhosis and diuretic resistant ascites. |
| **Design** | Investigator initiated, randomised, single blind, parallel arm, controlled trial. |
| **Blinding** | Due to the nature of the intervention and the primary outcome measure, we are unable to conduct the trial with blinding of the patients, the investigators or use blinded outcome assessment. |
| **Interventions** | Tunnelated peritoneal (PleurX) catheter versus large volume paracentesis. All patients will receive ciprofloxacin to prevent spontaneous bacterial peritonitis. |
| **Population** | We will include 32 adult patients with cirrhosis of any aetiology and diuretic resistant ascites. |
| **Sites** | Primary site: Gastro Unit, medical division, Hvidovre University Hospital, Denmark,  Gastrounit, medical division, Herlev University Hospital, Denmark, Department of medicine, Gastroenterology, Køge Hospital, Denmark, Department of Gastroenterology and Hepatology, Odense University Hospital, Denmark. |
| **Inclusion period** | 48 months. |
| **Follow up** | The total duration of follow up is six months. |
| **Primary Outcomes** | The primary outcome is paracentesis free survival. |
| **Secondary Outcomes** | Secondary outcomes include cumulative number of paracentesis, cirrhosis-related complications, safety, quality of life, changes in metabolic and biochemical parameters. |

|  | trial flow illustrated in flow chart | | | | | | |  |
| --- | --- | --- | --- | --- | --- | --- | --- | --- |
| **Prior to enrolment** | Identify eligible patients with ascites. Collect informed consent. | | | | | | |  |
|  |  |  |  | | |  |  |  |

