*Haemorrhage*: Less than 10% develop a local haematoma at the puncture site. More severe bleeding including peritoneal haemorrhage is described in the literature, but is very rare occurring in less than one percent.

*Hypotention, electrolyte and protein depletion*: The main risk associated with removal of ascites is hypotention, electrolyte and protein depletion. The risks occur after removal of at least four litres of fluid. Administration of albumin reduces the risk of these complications and is administered after removal of the first four litres (as described above). The risk is associated with the amount of fluid removed. Using the peritoneal catheter allows removal of smaller amounts of ascites (< 2 litres) and the risks of these complications are therefore negligible. To avoid electrolyte and protein depletion, patients in both interventions will be monitored with regular blood tests.

*Peritonitis*: Patients with diuretic resistant ascites have an increased risk of developing bacterial peritonitis. In addition, both interventions are associated with an increased risk of peritonitis. To reduce the risk of peritonitis, we will administer ciproxin prophylaxis to all patients.

*Bowel perforation*: Both interventions are associated with a potential risk of bowel perforation. The complication is very rare affecting less than one percent.

Risks associated with assessments of outcomes

The risks associated with blood sampling include local haematoma and pain.

The body composition will be assessed using dual-energy X-ray absorptiometry (DXA scan). The radiation associated with the scan corresponds to a conventional chest X-ray (0.02 mSv).

Potential Benefits

The potential benefits of the PleurX drainage system include improved management of ascites, quality-of-life, symptom management, and improved nutrition.

Primary Outcome Measure

- Paracentesis free survival

Secondary outcome measures

- Cumulative number of paracenteses
- Quality of Life
- Adverse events (as defined below under definition of adverse events and monitoring).

The assessment of outcome measures is described in Appendix A.

STUDY DESIGN

This trial will be conducted in compliance with the protocol, EN ISO 14155 ”Clinical investigation of medical devices for human subjects – Good clinical practice” and the applicable regulatory requirements.

Patient inclusion criteria

- Cirrhosis of any aetiology;

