- The PleurX Tunnelated Peritoneal Catheter is approved for permanent placement and catheter implantation is regular clinical practice prior to initiation of this study. Consequently the registration of medical device handling will include noting device LOT number in patient’s medical record and in the corresponding CRF.
- All peritoneal catheters are labeled with following information:
  - Manufacturers name and address: CareFusion, [name].
  - Exact description of package content.
  - Package content is STERILE.
  - LOT number.
  - Expiring date.
  - For single use only.
  - Warnings:
    - Do not use if package is damaged. Consult instructions for use. Contains phthalates.

Monitoring Procedures

Independent monitoring of the trial for clinical protocol and compliance will be conducted periodically (i.e., at a minimum of three monthly intervals) by qualified staff from the the GCP unit in the Capital Region. The sponsor-investigator will permit direct access to the study monitors and appropriate regulatory authorities to the study data and to the corresponding source data and documents to verify the accuracy of these data.

Other treatments

Other treatments that are considered necessary for the subject will be given at the discretion of the investigator. Administration of all other treatments will be recorded on the accompanying Case Report Form.

Procedures in case of emergencies

The investigator will ensure that the necessary procedures and expertise to handle emergency situations that may arise during the study will be available.

Adverse Events

Adverse events (AEs) are defined as any event, sign or symptom occuring during the study whether the AE is considered to be related to the intervention or not. All adverse events must be recorded in the patient's Case Report Forms.

If an AE occurs more than 1 week after the removal of the PleurX catheter or more than 1 week after completion of Visit 8, and there is no apparent causal connection or relation to the Pleurx catheter, this shall not be deemed to be an AE.

The median survival for patients with cirrhosis and diuretic resistant ascites is six months and mortality is therefore expected amongst study participants. Consequently fatal events due to chronic liver failure will not be categorised as a SADE.

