The primary outcome measure is paracentesis free survival. With an estimated probability of paracentesis free survival set to 0.3 at the end of the trial, an allocation ratio of 1:1, alpha 5% and power 80%, the required sample size is estimated to be a total of 28 patients (14 patients in each group). After taking into account the risk of participant dropout the sample size is set to be 32 patients (16 patients in each group).

Statistical analyses

We plan to include all patients randomised (intention to treat) regardless of compliance or follow up. Patient characteristics will be summarised using medians with interquartile range or proportions. Groups will be compared using t-tests or chi-square tests as appropriate. The level of significance will be set to 5%. The primary outcome measure will be evaluated using Kaplan Meier Plots and log-rank tests. Univariate and multivariate logistic regression analysis will be conducted to identify potential predictors of paracentesis free survival.

Handling of data

Data will be retrieved from medical records, information provided by the patients at trial visits as well as laboratory (biochemistry) assessments and investigational results. Data will be collected to Case report forms and entered into an electronic database by the principal investigator. Case report forms from the supporting sites will be sent by secure mail to the principal investigator. The database is anonymous. A trial participant identification list will be stored safely by the principal investigator.

Missing data

During the trial, we plan to search for information about missing data in the medical records. Investigators will pursue the options of repeating biochemistry and blood analyses when this is possible. Invasive procedures will not be repeated, should data be missing after the participant has completed the trial investigations.

Quality Control

The study personnel will be trained and tested in all study related procedures to ensure adequate quality control. In particular, investigators will be tested 0to ensure the optimal use of the interventions assessed (PleurX and large volume paracentesis). All investigators are specialised hepatologists with extensive experience in the management and observation of patients with refractory ascites including experience in the use of the PleurX and large volume paracentesis through their clinical work.

Data registration and rules for the control of investigation procedures

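### Events judged unrelated to the catheter lose adverse-event status one week after PleurX removal, a cut-off with no counterpart in the control arm

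*Protocol*

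**What the plan says.** The Adverse Events section first defines an AE as anything that happens during the study, "whether the AE is considered to be related to the intervention or not". The next paragraph adds an exclusion. It covers events that fall "more than 1 week after the removal of the PleurX catheter or more than 1 week after completion of Visit 8". Where such an event shows no evident causal link with the catheter, the rule is that "this shall not be deemed to be an AE".

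This definition feeds a trial outcome. The list of secondary outcome measures includes "Adverse events (as defined below under definition of adverse events and monitoring"), so the exclusion becomes part of the outcome definition. The synopsis states "The total duration of follow up is six months", and Visit 8 is on Day 180. Under Statistical analyses the protocol says "We plan to include all patients randomised (intention to treat) regardless of compliance or follow up".

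Three other provisions bear on the point:

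- The trial flow collects AE information at every visit to Day 180, and at admissions between visits. It makes no exception for patients whose catheter has been removed.
- The blinding section states that neither patients nor investigators can be blinded.
- The Adverse Events section lists events that it classes in advance as not associated with the catheter but still registers as AEs. Among them are admissions for large volume paracentesis and for chronic liver failure.

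**The concern.** The two time conditions are joined by *or*, and only one of them can arise in a control. A control's unrelated events count until one week after Visit 8. A PleurX patient's unrelated events count until one week after removal, if that comes first, even when months of follow-up remain. The arms then have different observation windows, and the difference depends on something that happens after randomisation.

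The direction is fixed: leaving events out can only lower the PleurX count. Removal is also not a random event. The Background gives infection, leakage and loculated ascites as reasons for it. Harm is half of the stated objective, and AEs are one of three listed secondary outcomes, so an uneven count bears directly on the safety comparison.

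**Working it through.** **Side by side.** In the definition, relatedness has no bearing on whether an event is an AE. In the exclusion, once a catheter has been out for more than a week, relatedness decides it. Both are current text in the same section. The pre-classified list shows the effect. An admission for chronic liver failure on Day 120 is registered as an AE in a control. In a PleurX patient whose catheter was removed on Day 60, the same admission is already classed as unrelated and therefore loses AE status.

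**When the removal condition matters.** If the catheter comes out at or after Visit 8, the Visit 8 condition has already closed the window for unrelated events, or closes it at the same time. Read literally, the removal condition changes something only when removal precedes Visit 8, which is within follow-up.

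**Inputs.** Visit 8 is on Day 180, so the full window ends on Day 187. There are 16 patients per arm (Sample Size Considerations). The removal rate is 0% to 7.5% (Background, from a review of PleurX in malignant ascites), or 0 to 1.2 of 16 patients. The protocol states no figure for this loss, so there is none to reproduce.

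**Formulas.** For removal on day *t*, share lost per patient = (187 − (*t* + 7)) / 187. Share lost in the arm = removal rate × that share. The working assumes a constant rate of unrelated events, no deaths and complete follow-up otherwise.

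| Removal day | Lost per patient | Arm loss at 7.5% removed |
|---|---|---|
| 30 | 150/187 = 80% | 6.0% |
| 60 | 120/187 = 64% | 4.8% |
| 90 | 90/187 = 48% | 3.6% |
| 120 | 60/187 = 32% | 2.4% |

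At a removal rate of 0% the loss is zero. Under these assumptions, a true rate ratio of 1.00 for unrelated events would appear as 1.00 to 0.94 (1 − 0.06) over the cited removal range.

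**If removal is more frequent in cirrhosis** (an assumption, since the protocol gives no rate): at 25% removed, the arm loss is 8% for Day 120 and 20% for Day 30. At 50% it is 16% and 40%.

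**After the fix.** With a common window to Day 187, the share lost through this rule is 0% in both arms.

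**The case against.** The strongest reply is that little is lost. Events linked to the catheter stay AEs without any time limit, so a late peritonitis attributed to the device is still counted. AE information is still gathered at every visit after removal, so the fault is one of classification and not of absent follow-up. A reader might infer that AE capture stops in the PleurX arm once the catheter is out. The text does not support that.

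This limits the point but does not remove it. Unrelated events are part of the defined outcome, and the duty to enter events in the case report form attaches to AEs. An event that is not deemed one need not be entered. The judgement of relatedness is unblinded, as is every such judgement in this open trial, but here it decides whether the event counts at all.

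A second reply is that the sponsor meant removal after the trial. The only removals the protocol plans for its own patients come after completion (Interventions; Visit 8). That intention is plausible, but the sentence carries no such limit, and read literally the removal condition would then be redundant.

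A third reply concerns size. A reader might take 2 of 16 catheters removed on Day 60 and arrive at 2 × 120 / (16 × 187) = 8.0%. That is a 12.5% removal rate, above the cited range. Moreover, if AEs are compared as proportions of patients, someone whose catheter was removed for a complication has probably been counted already, so lost window time overstates the effect on that measure. Both remarks stand.

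Two further inferences go too far. Nothing in the protocol shows that patients with a removed catheter are those most prone to later renal or hepatic events. Nor is there a formal breach of intention to treat: that sentence concerns which patients are included, and all of them are. The conflict is with the principle.

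**Conclusion.** The point holds as a contradiction within the Adverse Events section and as a one-sided AE window. Its direction favours the PleurX arm. For a patient with early removal the loss is large: 64% of the window for unrelated events at Day 60. For the arm it is about 0% to 4.8% at Day 60, and up to 6.0% at Day 30, over the cited removal range. That is roughly one patient of 16. The range comes from malignant ascites and the protocol gives none for cirrhosis, so the true size is uncertain. The figures also assume a constant event rate and no deaths.

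The primary outcome is unaffected and catheter-related events are retained. It should be fixed because the text is inconsistent and the bias has one direction, not because the expected loss is large.

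**What to change.** Use one AE window for both arms: from randomisation to one week after Visit 8, or to death if earlier, whatever has happened to the catheter. Delete the removal cut-off within follow-up, or limit it explicitly to catheters kept after Visit 8 and say which date governs. Within the common window, treat relatedness as a recorded attribute and not as a condition for being an AE; the section already requires it to be recorded. Keep the existing rule that device-related events count beyond the window.

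The cost is one sentence in the protocol and a matching line in the case report form instructions. No visits are added, because both arms are already seen to Day 180 with AE information collected each time. Events in the final week, to Day 187, are already within the rule for controls.

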Diuretic-resistant ascites is characterized by neuro-humoral activation of the sympathetic and renin-angiotensin-aldosterone systems as well as a low urinary excretion of sodium.^15-17^ Angiotensin II and norepinephrine increase sodium reabsorption in the proximal tubule and aldosterone in collecting tubules. The changes add to ascites formation and increase the risk of renal impairment and electrolyte disturbances. Increased levels of vasopressin result in an increased water retention relative to sodium retention, which means that patients often develop hypervolemic hyponatremia. The changes in the nervous system and vasopressors combined with the haemodynamic changes associated with portal hypertension increase the risk of renal impairment. The pathophysiology also involves an increased production of nitrous oxide and other vasodilators, which reduce the systemic vascular resistance.^18-20^ In the early phases, the cardiac output is increased to compensate for the changes.^21-23^ As the disease progresses the cardiovascular compensation becomes insufficient, ultimately leading to a decreased cardiac output and a reduced systemic blood pressure. The changes combined with increased activation of the renin-angiotensin system have deleterious effects on the kidneys. The treatment with diuretics further increases the risk of hyponatriemia and renal impairment, which are frequent causes of treatment discontinuation. *Hepatorenal syndrome* is a reversible renal failure that occurs in patients with cirrhosis and ascites.^2 6 20^ The diagnosis requires exclusion of other causes of renal failure such as acute tubulo-interstitial nephropathy and dehydration. The pathophysiology involves renal hypoperfusion associated with cirrhosis and portal hypertension. The decreased cardiac output and arterial vasodilation activate the systemic vasoconstriction as previously described. Infections such as spontaneous bacterial peritonitis may exacerbate the changes and therefore the risk of developing renal failure.^24^ The changes can lead to renal vasoconstriction and hepatorenal syndrome. In spite of treatment, the median survival is only three months.^25^

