Furthermore the listed parameters below occur regularly amongst patients with decompensated cirrhosis and ascites. They are thoroughly evaluated and afterwards categorized, by specialized hepatologists, as not being associated with carrying a permanent tunnelated peritoneal catheter. As a result this list of events will not be categorised at SAE but will be registered as AE:

- Hospitalisation du to large volume paracenthesis
- Alterations in type and dose of medicine
- Planned outpatient control visits due to other chronical diseases
- Hospitalisations due to chronic liver failure
- Hospitalisations due to alcohol intoxication
- Diagnosis of Hepatocellular carcinoma or other malignant diseases

Some side effects of ascites are obtained by letting the study participants answer the Quality of Life Questionnaire at every visit. Therefore these side effects will not also be listed as Adverse Events:

- Stomach pain or soreness
- Nausea
- Anorexia
- Reduced appetite
- Alterations in bowel habits
- Fatigue
- Dyspnoea
- Negative alterations in physical capability
- Leg pain

The type, potential relationship, severity, starts and end date for all AE must be recorded. The severity of the adverse event and the relationship with the study medical device must be assessed in accordance with the guidelines described below.

*The investigator must assess the relationship between an adverse event and the study medical device using the following guidelines:*

Adverse Device Effect (ADE): an adverse event related to the use of the medical device

Serious Adverse Event (SAE / pre-event): an event that results in i) death; ii) life-threatening injury or illness; iii) lasting harm to the body or bodily functions; iv) hospitalization or prolongation of existing hospitalization or required medical or surgical treatment are necessary to prevent i to iv.

Serious Adverse Device Effect (SADE): a serious incident which is related to the use of the medical device.

An almost-event is an equipment incident which does not have a serious output because of intervention before the event has evolved.

Serious incidents and near-incidents caused by improper treatment or error due to technical errors or defects in the equipment, instructions, labelling, use or maintenance of the equipment.

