A summary of product characteristics of the PleurX Peritoneal Catheter listed in the Investigational Brochure will be used as a reference document when it is assessed whether a serious related adverse event is expected or unexpected.

Grading of adverse events:

The investigator should attempt to identify all clinical and objective reactions from subjects and determine their relationship with the use of the allocated intervention (PleurX tunnelated catheter or repeated large volume paracentesis). Reactions, if there are any, should be graded according to the following scale:

1 = slight

2 = moderate

3 = severe

4 = life-threatening

Reporting of side effects of AEs and SAEs/SADEs

The investigator is responsible for ensuring that all adverse events are recorded in the patient's Case Report Form.

The sponsor is responsible for ongoing monitoring of the study's risk/benefit relation. The following must always be always immediately reported to the Danish Medicines Agency: any potential SAEs/SADEs and any situation that may affect the safety of the study subjects or the performance of the study. Similarly, reports should be made to all investigators and the Research Ethics Committees involved.

The sponsor shall at all time be kept informed by the investigator of any adverse events. At the end of the trial, the final report shall contain a description of all side effects.

Serious Adverse Device effect (SADE): Should be reported immediately by the investigator to the sponsor (sponsor-investigator). SADEs must be reported annually by the Investigator to the Research Ethics Committee throughout the whole trial period, together with a report on the safety of the trial subjects.

Fatal or life-threatening SADEs must be reported within 7 days of the sponsor becoming aware of them, and within 8 days of the report the sponsor must inform the Danish Medicines Agency of all relevant information on the follow-up.

All other SADEs should be reported to the same authorities within 15 days of the sponsor (sponsor-investigator) being informed of these.

All reports must be accompanied by comments on any consequences there are for the trial.

The sponsor (sponsor-investigator) will also inform the manufacturers of the medical device.

STATISTICS AND DATA MANAGEMENT

Sample Size Considerations

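### The protocol bars liver-failure deaths from being serious adverse device effects because they are expected, which conflicts with its own definition based on relation to the device

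*Protocol*

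**What the plan says.** The Adverse Events section first gives a reason: "The median survival for patients with cirrhosis and diuretic resistant ascites is six months and mortality is therefore expected amongst study participants". It then draws the rule: "Consequently fatal events due to chronic liver failure will not be categorised as a SADE". The rule carries no condition on whether the death is related to the catheter.

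Further down, the same section sets two definitions:

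- "Serious Adverse Event (SAE / pre-event): an event that results in i) death; ii) life-threatening injury or illness", so every death is an SAE.
- "Serious Adverse Device Effect (SADE): a serious incident which is related to the use of the medical device", so a serious event becomes a SADE through its relation to the device.

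The section also requires the investigator to assess and record that relation for adverse events. It separately lists events that are not treated as serious: "As a result this list of events will not be categorised at SAE but will be registered as AE". The item on that list closest to this point is "Hospitalisations due to chronic liver failure". Deaths are not on it.

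The section on reporting of AEs and SAEs/SADEs attaches some duties to SADEs alone. One is: "Fatal or life-threatening SADEs must be reported within 7 days of the sponsor becoming aware of them". Follow-up information to the Danish Medicines Agency is due within 8 days of that report, and SADEs go to the ethics committee every year. A more general rule in that section covers any potential SAE or SADE. These go at once to the Danish Medicines Agency, with similar reports to the investigators and ethics committees.

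**The concern.** One rule classifies a death by its relation to the catheter. The other classifies it by cause of death, and justifies this by saying that deaths are to be expected. A death can be both expected in the population and caused by the device, so the justification does not support the rule.

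The overlap is plausible on the protocol's own account. Under Potential Risks, both interventions are said to raise the risk of peritonitis. The Background adds: "Infections such as spontaneous bacterial peritonitis may exacerbate the changes and therefore the risk of developing renal failure", and says that these changes can end in hepatorenal syndrome. If a patient with catheter peritonitis then deteriorates and the death is attributed to chronic liver failure, two investigators could classify it differently while each follows the protocol.

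At stake is the SADE tally and the duties tied to it. Harms are part of the trial's objective, and adverse events are a listed secondary outcome. With 16 patients in the device arm, the fatal SADE result can turn on a single classification.

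**Working it through.** **Comparing the rules.** No stated figure needs reproducing, because the point concerns classification. Take a death attributed to chronic liver failure and judged related to the catheter:

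| Rule in the protocol | Result for this death |
| --- | --- |
| SAE definition (Adverse Events) | SAE, because it is a death |
| List of events downgraded to AE (Adverse Events) | Not affected; the list names admissions, not deaths |
| Assessment of relation (Adverse Events) | Required; assessed as related |
| SADE definition (Adverse Events) | SADE, because serious and related |
| Fatal-event sentence (Adverse Events) | Not a SADE |
| Immediate reporting of potential SAEs/SADEs (reporting section) | Applies |
| 7-day fatal-SADE deadline, 8-day follow-up, annual SADE report (reporting section) | Apply under the definition; do not apply under the fatal-event sentence |

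Rows four and five contradict each other, and the last row depends on which of them is followed.

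**Expectedness and relation.** Just before the grading scale, the protocol says that expectedness is judged against the device reference document for events already serious and related. There it is a later and separate judgement. The fatal-event sentence instead uses expectedness in the population to settle SADE status in advance.

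**Could the sentence mean unrelated deaths only?** An unrelated death already falls outside the SADE definition. On that reading the sentence would add nothing, and the qualifier is not in the text.

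**Size of one misclassification.** Input: 16 patients in the PleurX group (Sample Size Considerations). Exact (Clopper-Pearson) two-sided 95% limits:

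- Death excluded: 0/16 = 0%. Upper limit = 1 − 0.025^(1/16) = 20.6%.
- Death counted: 1/16 = 6.3%. Lower limit = 1 − 0.975^(1/16) = 0.2%. The upper limit solves P(X ≤ 1 | n = 16, p) = 0.025, which gives 30.2%.

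This shows what one such death would do. It does not predict that one will occur.

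**All-cause deaths, for scale only.** Assume exponential survival, so that expected deaths by six months = 16 × (1 − 0.5^(6/median)).

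- Median 6 months (protocol): 16 × 0.5 = 8.0.
- Median 9 months (assumed): 16 × 0.370 = 5.9.
- Median 12 months (assumed): 16 × 0.293 = 4.7.

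The longer medians allow for the inclusion criterion on expected survival of at least three months. The protocol gives neither the share of deaths due to liver failure nor the share related to the device, so the number of affected deaths cannot be derived.

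**The case against.** The strongest reply is that the sentence removes a label and little else. The death is still an SAE, its relation must still be recorded, and the immediate reporting rule is stricter than the 7-day one. Deaths also enter the primary outcome, paracentesis free survival. All of this stands. A reader might infer that device-triggered deaths go uncounted and unreported, or that nobody assesses their relation. The protocol does not support either inference.

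A second reply is that the wording attributes the death to the underlying disease, and that the next paragraph concerns events judged not associated with the catheter. That may well be the intention. But the judgement of no association is stated for the list that follows, not for the fatal-event sentence, whose stated reason is expectedness.

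A third reply is that the Background links peritonitis to renal failure and hepatorenal syndrome, not to chronic liver failure as such, and that serious catheter-related peritonitis would be a SADE in its own right. This is fair. The example depends on how the death is attributed, and the preceding infection would still be visible. The fatal outcome is what would be lost as a device effect.

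Two larger claims are tempting and should not be made:

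- That the rule covers most deaths in the PleurX arm. The protocol gives no breakdown by cause of death.
- That an affected death is likely because, at 10% per patient, at least one peritonitis case has probability 1 − 0.9^16 = 81%. That is the chance of peritonitis, not of a related liver-failure death. The 10% comes from an uncontrolled study counted per placement, in which some patients appear more than once and antibiotic use is unknown. All patients in this trial receive prophylaxis.

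**Conclusion.** The contradiction is real but narrow. For a liver-failure death judged related to the catheter, the SADE definition and the fatal-event sentence give opposite answers. If the sentence is followed literally, the death is misclassified. It leaves the SADE count and loses the 7-day deadline with its 8-day follow-up and the annual SADE report to the ethics committee. It remains a recorded SAE with relation assessed, and it stays under the immediate reporting rule.

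One such death would separate 0/16 (upper limit 20.6%) from 1/16 (6.3%, 95% CI 0.2 to 30.2%). The conclusion assumes that the sentence is applied as written, that the investigator judges the death related, and that its cause is recorded as chronic liver failure. How often these coincide cannot be known from the protocol. The sentence should be corrected because it affects how harm from the device is classified and the correction costs almost nothing.

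**What to change.** Reconcile the fatal-event sentence with the SADE definition and the reporting section. Either delete the sentence or limit it to deaths assessed as unrelated to the device. Possible wording: deaths due to chronic liver failure are recorded as SAEs and are expected in this population; each is assessed for relation to the device, and one judged related is classified and reported as a SADE, including when a device-related infection or other device complication preceded it.

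The cost is one sentence in the protocol. Assessment of relation is already required, so this adds little work for investigators. The downside is possibly one or two more expedited reports.
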